#### Measures

##### Overview

The measures selected for this study are listed in Table 1 [36,45-57]. There are three main categories of measures: setting and support features, rehabilitation-related recovery, and growth-related recovery. Although some measures have already been translated into some of the languages represented in this study, most measures had to be translated into most languages. The Consortium agreed to adopt standard translation-back translation procedures for cross-cultural research [58]. Questions or disagreements about translation were discussed among Consortium partners until they reached consensus.

**Table 1 table1:** Quantitative measures used for baseline (T0) and follow-up (T1) data collection.

Domain,Variables		Instruments
**Setting and support features**		
	Working alliance	Working Alliance Inventory—Participant (Horvath and Greenberg, 1989) [47]
	Service satisfaction	Self-Help Agency Satisfaction Scale (Segal et al, 2000) [46]
	Housing quality	Choice in Housing and Services (Srebnik et al, 1995) [45]
	Choice	Perceived Housing Quality and Choice/Control (Toro et al, 1997) [36]
**Rehabilitation-related recovery**		
	Housing status	European Typology on Homelessness and Housing Exclusion (FEANTSA^a^, 2005) [52]
	Psychiatric symptoms	Colorado Symptom Index (Shern et al, 1994) [48]
	Alcohol and drug use	Alcohol Use Disorders Identification Test (Babor et al, 2001) [49] Drug Use Disorders Identification Tool (Berman et al, 2005) [50]
	Physical health	General Self-Rated Health (DeSalvo et al, 2006) [51]
**Growth-related recovery**		
	Mastery	Mastery Scale (Pearlin and Schooler, 1978) [53]
	Capabilities	Capabilities Scale
	Recovery	Recovery Assessment Scale (Giffort et al, 1995) [54]
	Community integration	Community Integration Measure (Aubry and Myner, 1996; Segal and Aviram, 1978) [55,56]
	Distal social support	Distal Social Support Scale (Wieland et al, 2007) [57]

^a^FEANTSA: European Federation of National Organisations Working with the Homeless.

##### Setting and Support Features

Based on previous research on homeless services and theories of recovery, we identified four dimensions of service and support features to measure. These are subjective measures of service users’ perceptions of the setting that assess choice over housing and services [45], housing quality [36], satisfaction with involvement with services [46], and working alliances with service providers [47].

Objective setting features were identified from the literature on Housing First and staircase services, as well as our own experiences of these environments. These include the following service setting features: congregate or scatter-site housing, private or shared bedroom, private or shared bathroom, mixed or segregated gender, tolerate alcohol use on-site or not, tolerate drug use on-site or not, tolerate intoxication on-site or not, fixed length of stay or not, treatment required or not, set meal times or not, and curfews or not.

##### Rehabilitation-Related Recovery

For homeless adults, rehabilitation-related recovery is often conceptualized as successfully maintaining independent accommodation, decreased psychiatric symptom frequency, decreased problem-related alcohol and drug use, and improved physical health. We selected measures with established validity and reliability to measure these rehabilitation-related recovery indicators, which are listed in Table 1. Specifically, we included the Colorado Symptom Index [48] as well as measures of alcohol and drug use [49,50] and physical heath [51]. We also created a measure of housing status based on the European Typology on Homelessness and Housing Exclusion [52].

##### Growth-Related Recovery

Growth-related recovery in homelessness is also multidimensional, so we included a range of measures to capture the dimensions that are commonly the focus of key stakeholders’ attention. We included intrapersonal measures, such as mastery [53], hope, meaning of life, quality of life, and empowerment [54]. We also included interpersonal measures, such as community integration [55,56] and distal social support [57]. A measure of capabilities was developed and its content was validated for use in the Service Users’ Experiences Study. It consists of 54 items adapted from the capabilities framework [42] and the Acquired Capabilities Questionnaire for Community Mental Health [59].

#### Statistical Analysis

We plan to compare participants who are engaged in Housing First programs to participants engaged in traditional services to determine whether they differ on service and support features, rehabilitation-related recovery outcomes, and growth-related recovery outcomes at baseline and at follow-up. Based on previous experience [60] in which participants chose to skip items and even entire measures, we expect to have missing data on most measures. We also expect attrition at T1 because participants have died, cannot be located, or do not wish to complete the questionnaire a second time. We will use Little’s *missing completely at random* test to determine whether data is *missing completely at random*, *missing at random*, or *neither*. We will manage data that is *missing completely at random* or *missing at random* using one of two approaches, depending on the research question, statistical technique, and software package. In the first technique, we will use expected maximization imputation techniques [61]. We will employ this technique with cross-sectional analyses of variance and multiple regression with SPSS, version 24.0 (IBM Corp). In the second technique, we will employ maximum likelihood in multi-level modelling with Mplus, version 8.2 (Muthén & Muthén) [62].

We will use T0 data to control for differences at baseline while examining patterns of association at T1. As individual data will be nested within program data, we will use multi-level modelling to account for Level 1 and Level 2 differences in intercepts, slopes, and intercept-slope covariances while controlling for baseline scores, country of residence, and demographic factors. If there are significant differences in the intercepts or slopes for recovery outcomes, we will determine whether these differences are accounted for by program membership—Housing First versus traditional services—and setting features.

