#### Sample Size and Retention Plan

Our target sample for the second time point (T1) is 480 participants (Housing First, n=240, and traditional services, n=240). Because we anticipate attrition between T0 and T1, we intend to oversample each group at baseline. Based on prior research [22,36], we anticipate greater attrition in the traditional services group, so we aim to sample 38 Housing First participants and 45 traditional service participants in each of the eight countries at T0 (N=664). In order to maximize follow-up, we have adapted Stefancic and colleagues’ guidelines [44]. Specifically, at the baseline data collection meeting, researchers will ask participants to predict where they will be living 6 months later; to provide a range of contacts for family members, friends, and service providers; and to contact the research team if they change their phone number or move to a new residence. Participants will be compensated with a €20 shopping voucher for each questionnaire and interview they complete.

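### Little's test is asked to sort missing data into MCAR, MAR or neither, which it cannot do, and the choice to impute or use maximum likelihood is made to depend on that answer

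*Protocol article*

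**What the plan says.** Under Statistical Analysis, the protocol article expects two kinds of gap. One is skipped items and measures: "we expect to have missing data on most measures". The other is loss to follow-up: "We also expect attrition at T1 because participants have died, cannot be located, or do not wish to complete the questionnaire a second time". It then uses Little's "test to determine whether data is *missing completely at random*, *missing at random*, or *neither", and continues: "We will manage data that is *missing completely at random* or *missing at random* using one of two approaches". The first approach, for cross-sectional analyses of variance and multiple regression in SPSS, is EM: "we will use expected maximization imputation techniques". The second is likelihood-based: "we will employ maximum likelihood in multi-level modelling with Mplus, version 8.2". Which of the two applies depends on the research question, technique and software. No other criterion is given for telling MAR from neither.

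Under Sample Size and Retention Plan, the T1 target "is 480 participants (Housing First, n=240, and traditional services, n=240"). Baseline recruitment is 38 Housing First and 45 traditional participants in each of eight countries, 664 in all, because "we anticipate greater attrition in the traditional services group".

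**The concern.** Little's test compares the observed means of each missing-data pattern with the means expected under MCAR. It has two outcomes, reject or do not reject, and the plan needs three verdicts. The two that matter most, MAR and MNAR, differ only in how missingness depends on values nobody has seen. No test on the observed data can separate them without further assumptions.

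At stake is the T1 comparison of Housing First with traditional services, which is to inform policy recommendations. Both named methods rely on MAR. As written, the plan treats MAR as something the data will confirm, when it has to be assumed and then probed. The stated reasons for loss (death, loss of contact, refusal) could plausibly depend on unseen T1 housing, symptoms or substance use, so MNAR is a realistic possibility in this population.

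**Working it through.** **1. The plan's own figures.** T0: 8 × 38 = 304 Housing First and 8 × 45 = 360 traditional, and 304 + 360 = 664, as stated. With 240 per group at T1:
- Housing First loss: (304 − 240)/304 = 64/304 = 21.1%
- Traditional loss: (360 − 240)/360 = 120/360 = 33.3%
- Overall loss: 184/664 = 27.7%

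**2. Are these counts consistent with MCAR across groups?** For the 2 × 2 table of group by loss, chi-square = 664 × (64 × 240 − 240 × 120)² / (304 × 360 × 184 × 480) = 12.4 on 1 df, p = 0.0004. If attrition runs as the authors allow for, MCAR fails across groups before any test is done. Loss that differs only by group is still MAR once group is in the model.

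**3. What the test returns under known mechanisms.** Assumptions not in the document: one outcome with unit SD, T0–T1 correlation 0.6, T0 complete, no true group difference, logistic loss with slope 0.5 or 1.0 per SD, no clustering, no item-level gaps. Group sizes and loss rates are those of step 1. There were 2,000 simulated trials per row, tested at the 5% level. Little's statistic is d² = Σ nⱼ (observed mean − ML mean)ᵀ Σ̂ⱼ⁻¹ (observed mean − ML mean), summed over patterns j. It has 1 df on T0 and T1 scores alone and 2 df with arm added. The contrast comes from regressing observed T1 on T0 and arm, which equals maximum likelihood under MAR when only T1 is missing. Bias is given as absolute size.

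| Loss depends on | Slope | Rejects, arm left out | Rejects, arm included | Bias in contrast (SD) |
|---|---|---|---|---|
| Arm only (MAR) | – | 5–6% | 91% | 0.00 |
| T0 score (MAR) | 0.5, 1.0 | 100% | 100% | 0.00 |
| Unseen T1 residual, both arms (MNAR) | 0.5 | 5% | 89% | 0.05 |
| Same | 1.0 | 5% | 92% | 0.08 |
| Unseen T1 residual, traditional only (MNAR) | 0.5 | 4% | 91% | 0.13 |
| Same | 1.0 | 5% | 91% | 0.22 |

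Runs at this correlation put the last figure at 0.22 to 0.23. With correlation 0.5, the traditional-only range is 0.13 to 0.24.

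With arm included, the test rejects about 90% of the time both when loss depends on arm alone (no bias) and under MNAR (bias). With arm left out, it rejects at the 5% chance level under MNAR and always when loss depends on T0, where there is no bias. Neither version separates the cases.

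**4. Size of a departure from MAR, without the simulation.** If non-responders are d SD worse at T1 than MAR predicts, the contrast moves by d × (0.333 − 0.211) = 0.12d when this holds in both arms, by 0.333d in traditional services only, and by 0.211d (opposite direction) in Housing First only. For d = 0.5, an assumed value, these are 0.06, 0.17 and 0.11 SD.

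**The case against.** The strongest reply is that the test changes little. MCAR and MAR lead to the same two methods, and the choice between those does not depend on the test. The multi-level analysis already uses maximum likelihood with baseline scores, country and demographics, which is an MAR analysis. This largely stands. The verdict could alter the analysis only if data were declared neither. What remains wrong is that the licence for an MAR analysis is said to come from a test that cannot give it.

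Several stronger readings are tempting, and the documents do not support them:
- *That the rule will throw out a valid analysis.* The text does not say how a significant result is read. Read as neither, a valid MAR analysis would lose its licence. Read as MAR, an MNAR problem would be passed. Either reading is faulty, but the document does not commit to one.
- *That an MNAR study would be declared MCAR.* That follows only if arm is left out of the test. With arm in and attrition as planned, the test would usually reject. The article does not list the variables.
- *That the group contrast carries a large known bias.* When the same mechanism acts in both arms, an overall T1 mean can be off by 0.10 to 0.16 SD (slopes 0.5 to 0.8), but most of this cancels in the contrast. The larger contrast figures need MNAR loss in one arm only.
- *That 21% and 33% are stated attrition rates.* They are back-calculated from oversampling allowances.
- *That MNAR sensitivity analyses, or a method for the neither class, have been omitted.* A journal article may leave both to the full plan, so neither counts as a fault here.

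**Conclusion.** The sentence is wrong as written. It is operative text stating a rule, and no detail in an unseen analysis plan could make Little's test return the three-way answer it is assigned. The conflict with MCAR across groups follows from the article's own planned counts.

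The consequence is conditional. On the assumptions in the working, bias that the test does not identify is about 0.05 to 0.08 SD in the contrast if the same MNAR mechanism acts in both arms, and about 0.13 to 0.23 SD if it acts in traditional services only. The correlation, loss slopes, single outcome and absence of clustering are all assumed, so these values illustrate that the error can occur and do not estimate its size in this study. The point calls for correction because about 28% of T1 data are allowed to be missing, unequally by group, and the remedy is cheap.

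**What to change.** 1. Remove Little's test as a decision rule. Keep it, if at all, as a description of departure from MCAR, with the variables entered listed.
2. State MAR as an assumption. Use full-information maximum likelihood or multiple imputation for all comparisons whatever the test's p-value, with arm, country, program, T0 scores and recorded predictors of dropout in the model. This replaces single EM imputation, which yields one completed data set whose filled-in values are then analysed as if observed.
3. Add a delta-adjusted sensitivity analysis of the T1 contrast: shift non-responders 0 to 0.5 SD worse than MAR predicts, in both arms and in each arm alone, and report the shift at which the conclusion changes.

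The cost is a change of wording, a little more analysis work, and possibly a more cautious conclusion. No new data are needed if the predictors are limited to variables already in the analysis file. The tracing details gathered for follow-up may not be in that anonymized file, so their use should be checked before it is promised.

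### EM imputation followed by ordinary ANOVA or regression in SPSS treats filled-in values as observed data, which understates standard errors or, if programme type is left out of the imputation, shrinks the Housing First contrast

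*Protocol article*

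**What the plan says.** The Statistical Analysis section of the protocol article expects two kinds of missing data. For skipped items and skipped measures it says "we expect to have missing data on most measures", without giving a rate. For loss to follow-up it says: "We also expect attrition at T1 because participants have died, cannot be located, or do not wish to complete the questionnaire a second time".

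Data judged to be missing completely at random or missing at random are then handled in one of two ways. The first is: "In the first technique, we will use expected maximization imputation techniques". Its use is stated: "We will employ this technique with cross-sectional analyses of variance and multiple regression with SPSS, version 24.0 (IBM Corp". The second is maximum likelihood, for the multi-level models in Mplus. Nothing is said about multiple imputation, pooling or adjusted standard errors in the first branch.

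The same section plans to compare Housing First with traditional services on setting features and on both families of recovery outcomes, at T0 and at T1. The Sample Size and Retention Plan targets 240 participants per group at T1 and says "we aim to sample 38 Housing First participants and 45 traditional service participants in each of the eight countries at T0", because "we anticipate greater attrition in the traditional services group".

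**The concern.** EM imputation as usually run replaces each gap once with its expected value given the other variables. The completed file carries no record of which values were filled in, so ordinary ANOVA or regression on that file goes wrong in two ways:

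- The number of observations is overstated.
- The imputed points lie exactly on the fitted surface, so residual variance is too small.

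Both shorten the reported standard error. If programme type is not among the EM predictors, filled-in values in both groups are instead drawn towards a common mean, and the group difference is diluted.

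The comparison of Housing First with traditional services is the centre of the study, and the Discussion section intends the findings to support European policy recommendations. In the SPSS branch, one version of the EM model would declare too many differences and the other would report differences that are too small. The article does not say which version applies.

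**Working it through.** **Inputs from the Sample Size and Retention Plan**

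- T0: 38 × 8 = 304 Housing First and 45 × 8 = 360 traditional services, total 664. This reproduces the article's total.
- T1 target: 240 + 240 = 480.
- Implied loss (derived, not stated as a rate): 64/304 = 21.1%, 120/360 = 33.3%, overall 184/664 = 27.7%.

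**Assumed inputs**

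The article gives none of these: a two-sided 5% level, the T0–T1 correlation, the rate of skipped scales, the variables in the EM model, and whether a random residual is added. Simulations used 4,000 runs per setting, missingness completely at random, no true group effect (except where attenuation is computed) and no clustering by programme.

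**Case A: all 184 dropouts imputed by conditional means, programme type in the EM model, baseline-adjusted test**

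The estimate equals the completers' estimate, so:

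- True variance ∝ 1/240 + 1/240 = 0.008333.
- Reported variance ∝ (477/661) × (1/304 + 1/360) = 0.7216 × 0.006067 = 0.004378.
- SE ratio = √(0.004378/0.008333) = 0.725.
- Type I error = 2 × [1 − Φ(1.96 × 0.725)] = 15.5%. Simulation gives 14.6% to 15.8%, whatever the T0–T1 correlation.

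**Case B: same imputation, unadjusted T1 ANOVA**

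| T0–T1 correlation | Type I error |
|---|---|
| 0 | 15.5% |
| 0.3 | 13.5% |
| 0.5 | 12.3% |
| 0.7 | 9.0% |
| 0.9 | 7.0% |

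**Case C: as A and B, but with one random residual added to each imputed value**

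At correlations of 0.3 to 0.7, error is about 12.5% to 13.0% adjusted and 8.9% to 11.9% unadjusted.

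**Case D: all dropouts imputed, programme type left out of the EM model**

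Type I error is 4.9% to 5.7%, so there is no inflation. With equal numbers of completers, imputed values centre midway between the groups. If T0 scores do not themselves carry the group difference, the contrast is multiplied by 1 − 0.5 × 0.211 − 0.5 × 0.333 = 0.728. A true difference of 0.30 SD would be estimated as about 0.30 × 0.728 = 0.22 SD.

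**Case E: dropouts not imputed, EM used only for skipped scales, programme type in the model, correlation 0.5**

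With a share f missing in both groups, the SE ratio for the adjusted test is close to 1 − f, so the error is about 2 × [1 − Φ(1.96 × (1 − f))].

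| f (assumed) | Formula, adjusted | Simulated, adjusted | Simulated, unadjusted |
|---|---|---|---|
| 5% | 6.3% | 6.4% | 5.9% |
| 10% | 7.8% | 8.0% | 7.2% |
| 15% | 9.6% | 10.1% | 8.2% |

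**Comparison**

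In the same simulated data, analysis of the observed outcomes only has an error of 4.5% to 5.7%, which is nominal within simulation error. With a missing T1 outcome and complete predictors, the baseline-adjusted version of this analysis is what maximum likelihood gives.

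**The case against.** A reader might infer that, at the plan's own attrition, a 5% test at T1 simply runs at about 15%. The article does not support that, for three reasons.

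- It never says that dropouts' T1 scores will be EM-imputed. Oversampling at T0 so as to reach 480 at T1 rather suggests that those 480 are to be analysed, although the text on missing data lists attrition beside skipped items and does not settle the matter.
- At a realistic correlation, 15% needs a baseline-adjusted T1 test, and the article sends its baseline-controlled T1 models to multi-level modelling with maximum likelihood. A plain T1 ANOVA falls below 15% as soon as T0 scores are informative.
- It also needs programme type in the EM model and no added residual. Neither is stated, and such detail may properly be left to the analysis plan.

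A reader might also infer that nearly every result is affected. That goes too far: the multi-level analyses and the qualitative arm are untouched.

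The missing-data rates in Case E are assumptions. They also treat whole scale scores as missing, whereas a scale with one imputed item is mostly observed and would be affected less.

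All of this limits the size and the scope. It does not rescue the method. The choice of EM imputation before ordinary ANOVA and regression is stated in the article, not merely left undescribed. Every version of it examined with appreciable missing data gives either inflated error or a diluted contrast.

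**Conclusion.** The point holds for the SPSS cross-sectional branch only. A single EM-completed file analysed by ordinary ANOVA or regression does not give valid standard errors when programme type is in the imputation model, and gives an attenuated group difference when it is not.

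The size is conditional:

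- **Skipped scales only:** type I error of about 6% to 10%, for an assumed 5% level, 5% to 15% missing and a correlation of 0.5.
- **All T1 dropouts imputed, unadjusted ANOVA:** about 7% to 13.5% at correlations of 0.9 to 0.3.
- **All T1 dropouts imputed by conditional means, with a baseline-adjusted test or a correlation near zero:** about 15%, the top of the range.
- **Programme type omitted:** error near 5%, but the contrast falls to about 73% of its true size if all dropouts are imputed.

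The first three lines assume that programme type is in the EM model. Confidence is high that the method is unsound. The magnitude cannot be fixed from the article.

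**What to change.** Replace EM imputation for the cross-sectional comparisons with maximum likelihood in Mplus, which the plan already uses for its multi-level models. If these analyses must stay in SPSS, use multiple imputation with pooled standard errors, and include programme type, programme, country and T0 scores in the imputation model. In either case, state whether the T1 scores of participants lost to follow-up are part of what is being handled.

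The change affects analysis wording only: no new data, participants or design change. Intervals will be somewhat wider, and there is a little more analysis work.

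### Maximum likelihood is named for a contrast that varies only between programs; with few programs and a program ICC not near zero, its standard errors are too small

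*Protocol article*

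**What the plan says.** All of this is in the protocol article, mostly under Statistical Analysis.

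- **Estimator.** It is given as the second of two ways of handling missing data: "we will employ maximum likelihood in multi-level modelling with Mplus".
- **Clustering.** "As individual data will be nested within program data, we will use multi-level modelling".
- **Random part.** The models are to "account for Level 1 and Level 2 differences in intercepts, slopes, and intercept-slope covariances".
- **Adjustment.** They do so "while controlling for baseline scores, country of residence, and demographic factors".
- **Exposure.** Where intercepts or slopes differ, the authors will ask whether the differences are "accounted for by program membership—Housing First versus traditional services—and setting features".
- **Sample.** Under Sample Size and Retention Plan, the T1 target is 480 (240 per group). The baseline target is "38 Housing First participants and 45 traditional service participants in each of the eight countries at T0".

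The section Setting and Support Features lists four perceived features, measured on each person. It also lists objective features, such as curfews, required treatment and congregate or scatter-site housing.

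**The concern.** Whether someone is in Housing First or traditional services is a property of the program. The same holds for an objective setting feature wherever everyone in a program shares it. The precision of such an effect depends mainly on how many programs there are, not on 480 people.

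ML estimates the between-program variance as if the Level-2 fixed effects (intercept, service model, country) had cost nothing. The estimate is biased downwards, and the standard error of every program-level effect shrinks with it. With few programs, the main contrast and the objective setting features would be declared significant too often. The article says in its Discussion that these findings will support European policy recommendations on scaling up Housing First.

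**Working it through.** **The plan's own figure.** 8 × (38 + 45) = 664, as stated. The targets imply attrition of 1 − 240/304 = 21.1% in Housing First and 1 − 240/360 = 33.3% in traditional services. No inputs are given for the T1 target of 480, so it cannot be re-derived.

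**Inputs from the article.** N = 480 at T1, groups 1:1, eight countries, programs as Level 2, ML estimation, country adjusted for.

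**Assumptions.**
- Number of programs J from 16 upwards. Recruiting both models in each of eight countries gives a floor of 8 × 2 = 16.
- Balanced programs of m = 480/J people.
- Total variance 1, so τ² = ICC and σ² = 1 − ICC, with ICC 0 to 0.20.
- Random intercept only.
- Two-sided 5% level.
- Country as seven contrasts, giving p = 1 + 1 + 7 = 9 Level-2 fixed effects. The alternative without country contrasts has p = 2.

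**Formulas.** Let λ = σ² + mτ². The estimated contrast has variance 4λ/(mJ) = 4λ/480. Let SSB be the between-program residual sum of squares and SSW the within-program one. SSB is λ times a χ² on J − p df; SSW is σ² times a χ² on 480 − J df.

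- ML uses λ̂ = SSB/J. If that falls below SSW/(480 − J), it uses the pooled (SSB + SSW)/480.
- REML uses λ̂ = SSB/(J − p), with (SSB + SSW)/(480 − p) as its pooled value.

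**Check by hand.** When the ICC is large enough that pooling is rare, the ML standard error is too small by about √((J − p)/J).

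- J = 16, p = 9: √(7/16) = 0.661. The z test rejects when |t₇| > 1.96 × 0.661 = 1.296, which has probability 23.6%. With a t reference on 7 df the cut-off is 2.365 × 0.661 = 1.564, probability 16.2%.
- J = 48, p = 9: √(39/48) = 0.901. The z cut-off is 1.96 × 0.901 = 1.767 on 39 df, probability 8.5%. The t cut-off is 2.023 × 0.901 = 1.823, probability 7.6%.

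**Simulation with pooling** (400,000 draws per cell), seven country contrasts, ICC 0.05 to 0.20, type I error:

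| Programs | √((J−9)/J) | ML, z | ML, t on J−9 df | REML, t on J−9 df |
|---|---|---|---|---|
| 16 | 0.661 | 18–23% | 11–16% | 4–5% |
| 24 | 0.791 | 12–14% | 10–11% | about 5% |
| 32 | 0.848 | 10–11% | 8–9% | about 5% |
| 48 | 0.901 | 8–9% | 7–8% | about 5% |
| 64 | 0.927 | 7.0–7.5% | 6.4–6.9% | about 5% |
| 80 | 0.942 | about 7% | 6.2–6.5% | about 5% |

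**Milder settings, ML with z.**
- No country contrasts, ICC 0.05 to 0.20: 8.6–8.8% at 16 programs, about 6.7% at 32, about 6.1% at 48, 5.5–5.7% at 80.
- ICC 0.01, 16 programs: 8.7% with country contrasts, 6.4% without.
- ICC 0: 5.0–5.3% with country contrasts, 4.5–4.8% without.

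**Check with less tidy data.** This used unequal program sizes, a person-level baseline covariate and country indicators (ML with z, 2,500 draws per cell, ICC 0.05 to 0.20). It gave 19–24% at 16 programs, 11–12% at 32, 8–10% at 48, 6.5–7.6% at 80 and 5.6–6.5% at 128.

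Random slopes and program-level setting features were not simulated. The latter use further Level-2 degrees of freedom.

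**The case against.** The strongest reply is that the article names an estimator and nothing more. It gives no test statistic, reference distribution, degrees of freedom, alpha or small-sample correction, and a condensed article may leave these to the full protocol or SAP. A reader might infer that large-sample z tests are fixed; the text does not say so. This part of the reply stands, but it does not remove the problem. The ML variance is itself too small, so a t reference alone leaves 11–16% at 16 programs and 7–8% at 48. Only a different or corrected variance estimate brings the error back to about 5%.

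Other parts of the reply also stand and limit the claim:

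- **Number of programs.** It is not stated. The article refers to programs and services in the plural, so the count could be well above 16 to 32. At 120 programs with country contrasts the z test rejects only about 6%.
- **Eight countries are not eight clusters.** Programs are the Level-2 units. Eight matters only through the floor of 16 programs and the country contrasts.
- **ICC.** Participants are already in their program at T0, and the models condition on T0 scores. Lasting program differences may be partly absorbed, leaving a low residual ICC and little inflation.
- **Setting features.** A reader might extend the point to all of them. The four perceived features vary within programs, so the argument reaches only features that are the same for everyone in a program.

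**Conclusion.** The point holds conditionally. The article commits to ML for a contrast that varies only between programs, with country adjusted for, and ML understates the standard error of that contrast when programs are few and the program ICC is not near zero. On the stated assumptions the excess over 5% is large at 16 to 32 programs with country contrasts, moderate at 48, and small by 80. It is modest at any number of programs without country contrasts and essentially nil at ICC 0.

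The documents do not support the stronger statement that the study's standard errors are certainly too small. That depends on the number of programs, the ICC and the country coding, none of which is given. This is an analysis choice that should be changed, held with medium confidence.

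**What to change.** Keep the multi-level model. For continuous outcomes, test program-level effects by REML with Kenward-Roger or Satterthwaite degrees of freedom. If Mplus is kept, use a bias-corrected variance and refer program-level coefficients to a t distribution on the number of programs minus the number of program-level parameters. Report the number of programs per arm and country with the results.

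Costs:

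- **Wider intervals.** With country contrasts and a high ICC, the half-width grows by about 2.365/1.296 = 1.8 times at 16 programs and 2.023/1.767 = 1.14 times at 48, relative to ML with z.
- **Some conservatism at low ICC.** At ICC 0 to 0.01, REML with t on J − p df rejected 1.4–4.6% across 16 to 160 programs.
- **Missing data.** T1 outcomes missing at random given the model covariates need no imputation under REML. Missing T0 covariates would need multiple imputation if full-information ML in Mplus is given up. The authors expect gaps on most measures, so this is real work.
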